### Power and sample size calculation

Differences in clinically relevant treatment response for the primary outcome measure BAI is set at 4 points based on international academic literature for the BDI [67, 68], as academic literature on the BAI could not be found. International academic literature suggests that a standard deviation (SD) of 12 for the BAI can be used in the sample size calculation [36, 68, 69]. The intraclass correlation coefficient (ICC) is set at 0.04 based on a review on ICC for anxiety and depression and other mental disorders in primary care [70]. Sample size calculations based on these numbers show that 364 persons for each trial on panic disorder, generalised anxiety disorder and social phobia should be included in order to reject the null hypothesis that the intervention and control groups have improved their symptom level equally when the power is set at 0.8 and the significance level at 0.05.

Power calculations for the secondary outcomes have been estimated to be more than 0.8 based on calculations with 182 participants in each group (see Table 1). As we have not been able to find estimates for the BDI-II and the GAF-F for patients with anxiety disorders in general practice, estimates for patients with depression in general practice have been used as reference for power calculations for the BDI-II [36], whereas patients with social phobia recruited from psychiatric clinics have been used as reference for power calculations for the GAF-F [71]. Estimates for the SCL-90-R are based on a mixed anxiety and depression population in an outpatient setting [72].

**Table 1 Tab1:** Power calculations for the secondary outcomes

Secondary outcomes	Mean difference (MD)	Standard deviation (SD) of the pooled mean	Type 1 error	Calculated power
BDI-II	4 [77]	11 [36, 77]	5%	93%
GAF-F	5^a^	11 [71]	5%	99%
SCL-90-R	23 [72]	50 [72]	5%	99%

^a^For the GAF-F the expected mean difference has been conservatively estimated to be 5 points as this is considered clinically relevant

*BDI* Beck Depression Inventory, *GAF* Global Assessment of Functioning, *SCL* Symptom Checklist

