## Discussion

The design of the trials presents several strengths. The randomisation is carried out externally and is computer based which ensures an adequate allocation sequence and concealment, thus reducing the risk of (cluster) selection bias. In order to further limit the risk of selection bias, data will be analysed according to the intention-to-treat principle and attempts to increase follow-up rates will be made. Also, the trials are randomised at cluster level in an attempt to eliminate the potential risk of contamination otherwise introduced by individual randomisation. This risk could be present where GPs trained in collaborative care principles, and receiving supervision from a project psychiatrist, would not be able to differentiate between intervention and control patients when using their acquired skills and advice from the psychiatrist, which is likely to affect the results, and thereby making it more difficult to detect differences between the intervention and the control group. To ensure that the intervention is provided as intended, we monitor fidelity to the Collabri model at least twice during the intervention period.

The primary outcome is self-reported and patients are not blinded towards allocation, which might result in information bias and possibly overestimation of effects [75]. However, the BAI has been found usable for assessing the severity of anxiety symptoms in patients with anxiety disorders in a general practice setting [76], and other outcome measures will be assessor blinded for allocation; for example, the secondary outcome measure of psychosocial functioning (GAF-F). A limitation, as a result of the cluster-randomisation, may be that patients within a cluster have some similarity and may differ from patients from other clusters. However, sample size calculations including an ICC have been carried out, aiming to reduce this problem. Furthermore, we cannot be sure that all eligible patients are asked to participate by their GP, as patients are not systematically screened for eligibility.

The results of these trials will add to the limited pool of knowledge about collaborative care for patients with anxiety disorders. To our knowledge, they will be the first carried out in a Danish context and the first reporting results for generalised anxiety and social phobia separately.

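### Table 1 computes the secondary-outcome powers without the protocol's own ICC of 0.04; with it, BDI-II power is about 87% rather than 93%, and BAI at 15 months has no row

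*Protocol article*

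**What the plan says.** Under Power and sample size calculation, the protocol article takes a 4-point difference and an SD of 12 for the BAI, and adds: "The intraclass correlation coefficient (ICC) is set at 0.04". With power 0.8 and a significance level of 0.05 this leads to 364 patients per trial.

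For the secondary outcomes the same section says: "Power calculations for the secondary outcomes have been estimated to be more than 0.8 based on calculations with 182 participants in each group". Table 1 then gives, at a 5% type 1 error:

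| Outcome | Difference | SD | Stated power |
|---|---|---|---|
| BDI-II | 4 | 11 | 93% |
| GAF-F | 5 | 11 | 99% |
| SCL-90-R | 23 | 50 | 99% |

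The table has no ICC, design effect or number of clusters.

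Three other sections bear on this:
- Secondary outcome measures lists BAI at 15 months first; Table 1 has no row for it.
- Statistical analyses plans multi-level mixed models for the continuous outcomes, with GP as one of the levels, and anticipates unequal loss to follow-up.
- Feasibility plans for at least 48 GPs per trial, each recruiting seven to eight patients per disorder.

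**The concern.** The 182 per group is half of 364, and 364 is the number needed after inflation for clustering. If that number enters an ordinary two-sample formula as independent patients, the allowance for clustering is lost. The secondary outcomes come from the same patients in the same practices and are to be analysed with GP as a level, so their powers should carry a design effect as well.

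At stake is how a null secondary result is read. A reader who trusts 93% for BDI-II will take a null finding as stronger evidence against a 4-point difference than the design can give. The sentence on power also speaks of the secondary outcomes in general, while one of them, BAI at 15 months, is not shown at all. That outcome shares the primary outcome's instrument, and the primary was sized for 0.8 with no evident reserve.

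**Working it through.** **Inputs from the protocol article.** 182 per group; differences and SDs from Table 1; ICC 0.04; BAI 4 points and SD 12 (Power and sample size calculation); 48 GPs (Feasibility). A two-sided test is assumed, since sidedness is not stated. Equal cluster sizes are assumed.

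**Formula.** Power = Φ( MD / (SD × √(2 × DE / n)) − 1.96 ), with n per group and design effect DE = 1 + (m − 1) × ICC for m patients per GP.

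**Step 1: reproduce Table 1 with DE = 1, n = 182.**
- BDI-II: SE = 11 × √(2/182) = 1.153; 4/1.153 = 3.469; power 93.4%.
- GAF-F: 5/1.153 = 4.336; power 99.1%.
- SCL-90-R: SE = 50 × √(2/182) = 5.241; 23/5.241 = 4.388; power 99.2%.

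All three match the printed 93%, 99% and 99%.

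**Step 2: confirm that 364 already contains the ICC.** Without clustering, n = 2 × (12 × (1.96 + 0.8416) / 4)² = 141.3, so 142 per arm and 284 in all. With 8 patients per GP, DE = 1 + 7 × 0.04 = 1.28, and 284 × 1.28 = 363.5, hence 364. As a cross-check, the Table 1 method applied to the primary outcome (4 points, SD 12, 182 per group, DE = 1) gives 88.9%, where the section states 0.8 for the same patients. The section therefore uses two different methods.

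**Step 3: put the ICC into Table 1.** m = 364/48 = 7.58; DE = 1 + 6.58 × 0.04 = 1.263; effective n = 182/1.263 = 144 per group.
- BDI-II: SE = 11 × √(2 × 1.263/182) = 1.296; 4/1.296 = 3.086; power 87.0%.
- GAF-F: 5/1.296 = 3.858; power 97.1%.
- SCL-90-R: SE = 5.891; 23/5.891 = 3.904; power 97.4%.

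**Step 4: sensitivity to the number of clusters (BDI-II).** The article's alternative of 44 GPs and 374 patients has m = 8.5 and DE = 1.30, and gives 86.9%. Taking the 49 + 4 = 53 GPs reported as randomised, with 364 patients, gives 87.7%.

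**Step 5: BAI at 15 months.** The article gives no 15-month inputs, so 4 points, SD 12 and ICC 0.04 are carried over as an assumption. With full follow-up, SE = 12 × √(2 × 1.263/182) = 1.414; 4/1.414 = 2.829; power 80.8%.

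**Step 6: loss to follow-up.** No patient dropout rate is stated; the range is assumed. Loss reduces both n and m.

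| Assumed loss | DE | BDI-II | GAF-F | SCL-90-R | BAI, 15 months |
|---|---|---|---|---|---|
| 0% | 1.263 | 87.0% | 97.1% | 97.4% | 80.8% |
| 10% | 1.233 | 84.2% | 96.0% | 96.3% | 77.5% |
| 20% | 1.203 | 80.8% | 94.3% | 94.7% | 73.7% |
| 30% | 1.172 | 76.4% | 91.8% | 92.4% | 69.1% |

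Power falls below 80% at a loss of about 2.5% for BAI at 15 months, about 22% for BDI-II, and above 50% for the other two. None of these figures credits baseline adjustment or repeated measures.

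**The case against.** The strongest reply is that the stated conclusion survives. With the ICC included, every tabulated outcome stays above 0.8. GAF-F and SCL-90-R move by only about two points. The secondary powers do not set the sample size, and recruitment closed on 31 December 2016. All of this stands, and it confines the material error to the BDI-II cell.

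A reader might go further and infer that the claim of more than 0.8 is false for BAI at 15 months. The documents do not support that. With full follow-up the figure is 80.8%. It falls below 0.8 only under a loss rate the article never gives, or with a t reference on 46 degrees of freedom (79.1%), which the article does not mention. It also rests on 6-month inputs carried to 15 months. The planned mixed model could recover some precision. What remains is a missing row and a general claim with almost no margin for that outcome.

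A reader might likewise count the absence of a dropout allowance as part of the arithmetic error. It is a separate matter: the article says openly that 182 per group was used, and any loss rate is the reader's own assumption.

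Finally, the Discussion's remark that "sample size calculations including an ICC have been carried out, aiming to reduce this problem" could be read as contradicting Table 1. It is true of the primary calculation and says nothing about secondary power, so no contradiction is claimed.

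The replacement values are themselves conditional. The article states a minimum of 48 GPs, not 24 clusters per arm; a cluster is a provider number that may cover several GPs; and the ICC of 0.04 comes from a review of anxiety, depression and other mental disorders, so its use for GAF-F is an assumption. Step 4 shows that the cluster number matters little.

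**Conclusion.** The powers in Table 1 are wrong for a cluster-randomised design with the article's own ICC. The size is modest: BDI-II about 87% instead of 93%, so a type II error of about 13% instead of 7%; GAF-F and SCL-90-R about 97% instead of 99%. These values assume ICC 0.04 for every outcome, about 48 equal clusters, a two-sided 5% test and full follow-up. The statement that power exceeds 0.8 holds for all three tabulated outcomes on that basis.

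For BAI at 15 months the table is silent. On carried-over inputs the claim holds only with near-complete follow-up. This calls for a reporting correction; it does not challenge the sample size of 364.

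**What to change.** - Replace the power column of Table 1 with cluster-adjusted values: BDI-II 87%, GAF-F 97%, SCL-90-R 97%.
- State beneath the table the ICC, the number of clusters and the follow-up assumption behind those values.
- Add a row for BAI at 15 months with its assumed difference, SD and ICC. If the primary outcome's inputs are used, this is about 81% with no loss; show it also at the follow-up rate expected at 15 months.
- Reword the sentence claiming power above 0.8 so that, for BAI at 15 months, it is conditional on near-complete follow-up. If any gain from baseline or repeated measures is counted, state the correlation assumed.

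The cost is one table and one sentence. Recruitment, conduct and analysis are unchanged; the printed powers become slightly less favourable.

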### Statistical analyses

Data analyses will be carried out according to the statistical principle ‘intention-to-treat’ [73]; thus, once a person meeting the eligibility criteria is included in the study the person stays in the study population, including follow-up, regardless of whether the person later meets the exclusion criteria. All continuous outcome measures will be analysed using generalised linear models. Multi-level, linear mixed models with repeated measures will be used to handle the cluster-randomisation and unequal loss to follow-up. The models will be estimated using an unstructured covariance matrix if possible. If not possible, other covariance matrices, such as independent, interchangeable, autoregressive, and Toeplitz, will be estimated, and the best fitting structure selected based on Bayes’ information criterion. The analysis levels are: GP, patient and time. This model is based on the assumption that data are missing at random or missing completely at random. Explorative subgroup analyses will be made for patients with somatic comorbidity and personality disorders.

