### Exclusion criteriaRecruitment and randomisation

#### Cluster level

The GP recruitment period lasted from May 2014 until July 2015. GP practices were invited to participate via postal letters. This included easy-to-read information about the project and an invitation to attend information meetings. Eligible GPs were randomised to either provide treatment according to the Collabri model or treatment-as-usual. A cluster corresponds to a GP provider number which may include one or several GPs. Cluster-randomisation was chosen, as a significant risk of bias was identified in the form of contamination if randomisation was performed on patient level. Randomisation was performed externally by The Research Centre for Prevention and Health (RCPH) in the Capital Region of Denmark, which used a centralised computer-generated allocation sequence. The randomisation was conducted in two phases. The first included 49 GPs and was stratified by three geographically defined uptake areas. The second randomisation included four GPs, and here a geographical stratification was not used.

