#### Individual level

As the trial is randomised on general practice level, the participating patients are allocated to either the intervention or control group according to their GP. The GPs identify and recruit the patients with anxiety disorders. In Danish medical guidelines GPs are recommended to use the Anxiety Symptom Scale (ASS) in conjunction with *ICD-10* criteria for diagnostic investigation [24]. The GP provides written and verbal information about the project, and hands out the Consent Form. Following recruitment, a research assistant contacts the patient to schedule a telephone baseline eligibility interview. The aim is to assess inclusion and exclusion criteria and verify the GP’s diagnosis by conducting a diagnostic interview. If the diagnosis according to the diagnostic interview differs from the diagnosis given by the GP, the research assistant consults a psychiatrist in the Collabri team who contacts the GP in order to discuss and agree on the diagnosis. Patient recruitment was initiated in November 2014 and ended on 31 December 2016.

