##### Primary outcome measure

The primary outcome is anxiety symptoms measured with the Beck Anxiety Inventory (BAI) 6 months after baseline. The BAI is a 21-item general questionnaire for anxiety, measuring symptoms during the last week rated on a four-point Likert-scale from 0 (never) to 3 (almost all the time), where the maximum score is 63 [45]. The BAI has shown excellent psychometric properties, with internal consistency: *α* = 0.92 and 1-week test-retest reliability: *r* = 0.75 in a community sample [46].

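### The primary contrast is a 6-month BAI level in one section and equal improvement in another. The article does not say how baseline BAI enters, although unblinded GPs recruit after allocation.

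*Protocol article*

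**What the plan says.** All references are to the Protocol article.

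- **Outcome (Primary outcome measure).** "The primary outcome is anxiety symptoms measured with the Beck Anxiety Inventory (BAI) 6 months after baseline". This is a level at one time point. Under Outcome measures, questionnaires are completed at baseline, 6 and 15 months.
- **Null hypothesis and sizing (Power and sample size calculation).** The hypothesis to reject is that "the intervention and control groups have improved their symptom level equally", which is a statement about change. The inputs are those of a level: "Differences in clinically relevant treatment response for the primary outcome measure BAI is set at 4 points", and "a standard deviation (SD) of 12 for the BAI can be used in the sample size calculation". No baseline correlation is given.
- **Model (Statistical analyses).** "Multi-level, linear mixed models with repeated measures will be used to handle the cluster-randomisation and unequal loss to follow-up". The levels are GP, patient and time. No fixed effects are listed. Intention-to-treat is defined as keeping an eligible person in the study population once that person has been included.
- **Randomisation (Recruitment and randomisation, Cluster level).** The first batch of 49 GPs was "stratified by three geographically defined uptake areas". A second batch of four GPs was not stratified.
- **Recruitment (Individual level; Blinding; Exclusion criteria).** "The GPs identify and recruit the patients with anxiety disorders". A patient's arm follows from the GP's arm, and GPs are not blinded. The research assistants who check eligibility are blinded. One exclusion, concerning patients who prefer the public psychologist scheme, is written for the intervention group only.
- **Bias control (Discussion).** "In order to further limit the risk of selection bias, data will be analysed according to the intention-to-treat principle", together with efforts to raise follow-up.

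**The concern.** If the two arms had the same expected baseline BAI, equal improvement and equal 6-month level would be the same null hypothesis, and the difference in wording would affect only precision. This design does not secure that equality. Randomisation was at practice level, patients are found afterwards by GPs who know their arm, there is no systematic screening, and one exclusion operates in one arm only. Baseline severity could therefore differ systematically between arms. A raw 6-month difference would then carry part of that imbalance into the effect estimate. A simple difference in change would overcorrect, in the opposite direction. The article's text allows either.

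Precision is also at stake. The sample size rests on the variance of a level. A change contrast has a larger variance than that when the baseline-to-follow-up correlation is below 0.5, whereas conditioning on baseline never has a larger one.

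The Discussion offers intention-to-treat against selection bias without saying which kind. By the article's own definition it acts only on people already included, so it cannot affect who was recruited.

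**Working it through.** **Inputs from the article.** Difference 4, SD 12, ICC 0.04, power 0.8, significance level 0.05 (taken as two-sided), 182 per arm, 48 GPs per trial (Power and sample size calculation; Feasibility).

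**Assumptions, not in the article.** The correlation r between baseline and 6-month BAI is taken from 0.3 to 0.7. A baseline imbalance d of 2 points (intervention minus control) is used for illustration. BAI variance is the same at both occasions, the variance factors apply equally between and within clusters, data are complete, and the normal approximation is used.

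**Step 1: reproduce the plan's figure.** The rule 16 x SD² / difference² gives 16 x 144 / 16 = 144 per arm, so N0 = 288. With k clusters, N = N0(1 - ICC)k / (k - N0 x ICC):

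- k = 48: 288 x 0.96 x 48 / (48 - 11.52) = 363.8 (article: 364).
- k = 44: 288 x 0.96 x 44 / (44 - 11.52) = 374.5 (article: 374).

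The exact normal formula (142 per arm) gives 357 and 368. The plan's size is therefore that of an unadjusted level contrast; no r is needed to obtain it.

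**Step 2: power of the three contrasts at N = 364.** Design effect = 1 + (364/48 - 1) x 0.04 = 1.263. Standard error for a level = 12 x sqrt(2 x 1.263/182) = 1.414. Power = Phi(4 / (1.414 x sqrt(v)) - 1.96), where v is 1 for the raw level, 2(1 - r) for change, and 1 - r² with baseline adjustment. Example at r = 0.4: for change v = 1.2, giving 0.733; for adjustment v = 0.84, giving 0.870; for the raw level, 0.808.

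**Step 3: bias from a 2-point imbalance when there is no true effect.** Raw 6-month contrast: r x d. Unconstrained change contrast: r x d - d = -(1 - r) x d.

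| r | Bias, raw level | Bias, change | Power, raw level | Power, change | Power, adjusted |
|---|---|---|---|---|---|
| 0.3 | +0.6 | -1.4 | 81% | 67% | 84% |
| 0.4 | +0.8 | -1.2 | 81% | 73% | 87% |
| 0.5 | +1.0 | -1.0 | 81% | 81% | 90% |
| 0.6 | +1.2 | -0.8 | 81% | 89% | 94% |
| 0.7 | +1.4 | -0.6 | 81% | 95% | 98% |

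As shares of the 4-point target, 0.6/4 = 15% and 1.4/4 = 35%. If the imbalance ran the other way, all signs would reverse.

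**Step 4: effect on the test.** At r = 0.5 the bias is 1.0 in absolute value, and both contrasts have standard error 1.414, since v = 1 for each. The two-sided type I error is 1 - Phi(1.96 - 0.707) + Phi(-1.96 - 0.707) = 0.109, about 11% against a nominal 5%.

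**Step 5: check of the remedy.** A simulation had 182 patients per arm, r = 0.5, d = 2, no true effect, no clustering, 400 replicates, and imbalance only in measured baseline BAI. The mean estimate was 1.03 for the raw level, -1.04 for change, -0.01 for analysis of covariance, and 0.00 for a repeated-measures model with a common baseline mean.

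**Step 6: the stratum term.** The article gives no between-area variance, so no figure can be computed. Leaving out a stratification factor does not bias the contrast and usually only makes the standard error somewhat too large.

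**The case against.** The strongest reply is that the article condenses a longer protocol. Its analysis section lists no fixed effects at all, not even arm or visit, and such lists are commonly left to the full protocol or the analysis plan. A reader might infer that the primary model has no baseline term. The text does not support that: baseline is a measured occasion and time is a model level, so baseline BAI may well enter, and with a common baseline mean the bias shown above would disappear. This stands. Silence about covariates is not an error in itself. What remains is that two sections of the article describe different primary contrasts and that the stated model does not decide between them.

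Second, the null hypothesis under Aim and design speaks only of the same effect on anxiety symptoms, and the improvement wording may be loose phrasing. That is possible, but it is the wording attached to the sample size, and it coincides with a level contrast only if expected baselines are equal.

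Third, the harms of the raw and change contrasts are alternatives and cannot both occur, and they rest on an assumed r and imbalance. With r above 0.5 a change contrast is more powerful than the raw level, and the raw level itself meets the planned 80%. All of this stands.

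Fourth, a reader might infer that the article claims intention-to-treat controls recruitment bias. It claims less: it speaks of further limiting risk, pairs this with follow-up efforts (which fits attrition), refers to concealment at cluster level, and admits that not every eligible patient may be asked. Blinded eligibility interviews with diagnostic verification are a real, partial safeguard, though they see only patients the GP has already put forward. The article still does not say that recruitment could differ by arm, nor that intention-to-treat cannot address it.

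**Conclusion.** The point holds as an inconsistency in the stated primary contrast, together with an imprecise account of bias control. It does not show that the analysis will be unadjusted or that imbalance will arise.

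If a 2-point imbalance did arise, the choice the article leaves open would move the estimate by 15% to 35% of the target difference, in opposite directions for the two readings, while conditioning on baseline would bring it to about 0. The change reading would have less than the planned power for r below about 0.5. Baseline adjustment would raise power above that of the raw level throughout the assumed range. These figures depend on the assumed r and imbalance and on imbalance acting through measured BAI. Adjustment cannot remove unmeasured differences in who was recruited. The stratum term is a minor matter of precision.

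**What to change.** 1. State one primary contrast: the arm difference in mean BAI at 6 months from the mixed model, conditional on baseline BAI. This can be done with baseline-by-visit terms and the 6- and 15-month scores as outcomes, or with baseline as an occasion and a common baseline mean across arms.
2. Reword the null hypothesis under Power and sample size calculation to match. The 364 need not change, because it was derived without relying on adjustment.
3. As a minor addition, include the randomisation stratum: three areas, with the second batch of four GPs as its own level.
4. In the Discussion, say that intention-to-treat addresses exclusion and attrition after inclusion only. Name recruitment by unblinded GPs after allocation, and the intervention-only exclusion, as a separate limitation that baseline adjustment reduces only for measured BAI.
5. Report recruitment and exclusion counts per arm.

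The cost is wording and a few degrees of freedom. Baseline BAI is already collected and the strata are known from the randomisation.
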